### Recruitment and consent

Services will be asked to identify potentially eligible young people, share information about the trial, and determine whether they are happy to be contacted by the research team. For young people aged under 16 years, a parent or guardian will also need to agree to them being contacted by the research team. The service can then refer the young person to the study team. Clinical services (e.g. CAMHS) may identify potentially eligible young people at various points including through review of waiting lists and service records. Referred young people will be screened by a researcher for eligibility and, if eligible and interested in participating, invited to take part in a baseline assessment. Baseline assessment meetings will either be in person or online via video call, depending on practicability and preference. Informed consent would be taken at the start of the baseline assessment meeting by a researcher (who will receive training in consent taking). For those aged under 16 years, consent from a parent or guardian along with assent from the young person would be sought, whilst only consent from the young person will be required for those aged 16 or 17 years. If the meeting is in person, then a physical consent form will be used. If the meeting is occurring online, then an audio-recorded verbal consent process will be used whereby a researcher takes the participant (and their parent or guardian if required) through a consent script and records their responses on an encrypted device. The study team will contact and share information about the study with local schools, colleges, and CAMHS within the recruitment area, raising awareness of the study. We will focus on contacting services and institutions in socioeconomically deprived areas and demographically diverse areas in particular, to try and encourage participation from these locations, given that health inequalities can affect participation in research trials [30].

### Baseline characteristics

During the baseline assessment participant demographic information (age, gender, ethnicity) and clinical history (past and current physical and mental health diagnoses, receipt of psychological therapy, and medication use) will be recorded in order to characterise the sample. Sexual orientation will also be recorded if known, given that self-harm rates are elevated amongst sexual minority groups [31, 32]. We will also record socioeconomic deprivation based on current postcode using the Indices of Multiple Deprivation [33], as this is another important risk factor for self-harm. The MINI-KID [29] will be used to determine mental health presentation. This is a structured interview that assesses past and current mental health difficulties. Only the modules relating to depression, common anxiety disorders (panic disorder, social anxiety, generalised anxiety disorder), bipolar disorder, and psychosis will be used to minimise burden.

### Primary outcomes

The primary trial outcomes relate to feasibility and acceptability. Data on recruitment rates, participant retention at follow-up assessments, missing data, and adherence (i.e. attendance at therapy sessions) will be recorded and evaluated against a set of pre-specified progression criteria (see Table 1). These criteria will indicate whether progression to a definitive trial is warranted, using a traffic light system (green = progress to larger trial; amber = modification needed; red = do not progress). Acceptability will also be evaluated via the qualitative process analysis. Levels of missing data and qualitative data will guide decisions about the most appropriate primary outcome for an efficacy trial. It is anticipated that self-harm urges, assessed via the Alexian Brothers Urges to Self-Injure scale (ABUSI; [34]), or behaviour, assessed via the Self-Injurious Thoughts and Behaviours Interview Short Form (SITBI; [28]), would be the primary outcome in a subsequent trial. However, the suitability of these outcomes would be evaluated based on statistical considerations and participant feedback plus guidance from the Patient and Public Involvement (PPI) advisory group.

**Table 1 Tab1:** Progression criteria

Outcome	Criterion	Green	Amber	Red
Recruitment	Ability to randomise 60 participants in a 12-month recruitment window	≥ 80%	60%—79%	< 60%
Retention	Percentage of participants attending the 16-week assessment as the potential primary outcome timepoint	≥ 75%	60%—74%	< 60%
Outcome Suitability	Missing data on candidate primary outcomes (SITBI, ABUSI) at 16-week assessment	≤ 15%	16%—25%	> 25%
Adherence	Percentage of participants receiving the minimum dose of therapy (≥ 4 sessions) within 16-week treatment window	≥ 75%	60%—74%	< 60%

### Clinical outcomes

A range of assessments of clinical outcomes will be taken, covering self-harm behaviour and urges, depressive symptoms, perceived recovery, internalising and externalising problems, and perceived dependence on self-harm. Table 2 presents a summary of the timing of study assessments. Data will be checked for missing data, and floor and ceiling effects for these measures which may affect their inclusion in a larger trial. Participants’ experience of completing measures, ascertained from the qualitative process evaluation, will also inform decisions.

**Table 2 Tab2:** Overview of assessment schedule

Measure	Baseline	8 weeks	16-weeks	20-weeks
ABUSI	x	x	x	x
AEP				x
Bespoke service use measure	x			x
CHU9D	x			x
ESIQ	x	x	x	x
MINI-KID	x			
PHQ-A	x	x	x	x
ReQuestYP	x	x	x	x
SDQ	x	x	x	x
SITBI	x	x	x	x

*ABUSI* Alexian Brothers Urges to Self-Injure scale, *AEP* Adverse Experiences in Psychotherapy questionnaire, *CHU9D* The Child Health Utility Instrument, *ESIQ* The Experiences of Self-Injury Questionnaire—Positive Beliefs subscale, *MINI-KID* Mini International Neuropsychiatric Interview for Children and Adolescents, *PHQ-A* The Patient Health Questionnaire—9 for adolescents, *ReQuestYP* The Recovery Questionnaire, *SDQ* Strength and Difficulties Questionnaire, *SITBI* Self-Injurious Thoughts and Behaviours Interview

#### Self-harm behaviour and urges

The SITBI short form [28] is a structured interview measure that will be used to assess suicide attempts and non-suicidal self-injury (NSSI). Sections of the measure will be adapted in line with the revised version of the SITBI [35] to improve the clarity of questions. Specifically, the opening question about NSSI will use the wording from the revised SITBI that provides additional detail on what might be considered as NSSI and some examples of behaviours that would not count as NSSI including indirect forms of harm (e.g. starving oneself). The ABUSI [34], a 5-item questionnaire, will be used to assess urges to self-harm over the past week. Scores range from 0 to 30 with higher scores indicating more severe urges. The validity and reliability of both measures have been demonstrated with young people [28, 34].

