## Introduction

Self-harm, encompassing acts of self-injury and overdose irrespective of suicidal intent [1], often starts during adolescence with self-harm amongst young people increasing in recent years [2–6]. A meta-analysis of global self-harm rates in children and adolescents suggests a lifetime prevalence of 14% [7]. The occurrence of self-harm behaviour is associated with an increased risk of future self-harm and suicide, as well as physical and mental health difficulties [8–11]. Whilst there is evidence that psychological approaches can help young people who self-harm, this evidence remains scarce [12, 13]. Effective intervention with young people who self-harm may prevent further occurrence and escalation of these difficulties. Given the growing pressures facing child and adolescent mental health services (CAMHS; [14]), brief intervention holds the promise of filling gaps in service provision and enabling more rapid access to therapy.

One potential brief therapy that could be helpful for young people who self-harm is brief cognitive analytic therapy (CAT). Cognitive analytic therapy (CAT; [15]) is a time-limited, relational therapy, which has already been investigated as an approach for young people with complex difficulties [16–18]. brief CAT has been developed as an 8-session approach and already investigated in adults who self-harm [19]. However, there are currently no trials of brief CAT for young people who self-harm. CAT is usually 16 or 24 sessions long. The 8-session format of brief CAT was guided by the recognised value of shorter interventions in reducing waiting times and the additional benefit to young people in fitting around education and other commitments.

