### Trial setting and participants

The trial will take place across three large and demographically diverse NHS Trusts in the North of England. Participants will be young people with experiences of self-harm who will be recruited through CAMHS and associated services (e.g. mental health in schools’ teams, other outpatient psychology services for young people).

Participants will be required to meet the following inclusion criteria:Aged 13–17 years.Engaged in self-harm, following the NICE definition [1], two or more times in their lifetime, with at least one episode in the past year. This will be confirmed via the Self-Injurious Thoughts and Behaviours Interview Short Form (SITBI; [28]).Can be safely seen in an outpatient clinical context in which treatment is being provided as judged by their clinical team or referrer.

Exclusion criteria will be as follows:Moderate-to-severe intellectual disability (IQ: < 70) as judged by a young person’s clinical team.Organic cerebral disease/injury affecting receptive and expressive language comprehension as judged by a young person’s clinical team.Currently an inpatient.Currently experiencing an active episode of mania or psychosis, assessed with the Mini International Neuropsychiatric Interview for Children and Adolescents (MINI-KID; [29]).Judged at imminent risk of harm to themselves, operationalised as presence of intent or planning to end their lives within the near future (e.g. next 2 weeks). In such cases, individuals could still participate once the level of risk has declined.Currently receiving another active one-to-one psychological therapy. This would include structured psychological therapies such as CBT or DBT. Other forms of support, like a support group or skills group, seeing a clinician for informal support or medication advice, or engaging with self-help materials, will not exclude people.

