### Statistical analysis

As this is a feasibility study, we will report descriptive data on study ‘processes’ and ‘outcomes’. An intention-to-treat (ITT) protocol will be followed. Descriptive data concerning recruitment, retention, and attrition will be presented in a CONSORT flow chart [58]. Treatment engagement and attrition rates will be calculated with associated confidence intervals and reasons for leaving the trial or therapy early will be reported where available. Rates of missing data will be presented for outcome measures. Descriptive statistics will be presented for the overall sample and by group for all potential outcome measures. RELATE-YP is a feasibility study and inferential testing of treatment efficacy is therefore not the goal of the study. Nonetheless, we will estimate treatment effects and associated confidence intervals to inform planning for a future trial. These analyses will use an appropriate regression model, depending on the distribution of the outcome variable (e.g. linear regression for continuous outcomes, negative binomial regression for count outcomes). A detailed SAP will be drafted by the trial statistician and approved by the TSC prior to any analyses taking place. This will be available from the research team on request. No interim analyses are planned. Imputation may be used to generate total scores on scales where < 20% of items are missing but will not otherwise be used.

For the feasibility economic analysis, the extent of missing cost and outcomes data will be presented using descriptive statistics. The CHU9D will be used to derive quality-adjusted life years (QALYs), in line with National Institute for Health and Care Excellence (NICE) reference case [59]. The cost of delivering the intervention will be estimated based on the resources used as recorded by trial therapists. Published NHS and social care unit costs will be attached to these estimates of resource use. The identity and quantity of other health and social care resources used by participants will be captured and summarised. This information is required for a full economic evaluation and will be used to understand what services participants access as TAU to help define exemplar comparators for a future cost-effectiveness analysis. Data on what participants received as TAU will be presented in our final reporting and reviewed holistically to help inform the planning of a future definitive trial.

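### As described, the SITBI gives overdose without suicidal intent no stated place, although the plan's own definition of self-harm includes it

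*Protocol article*

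**What the plan says.** The article's Introduction sets the construct: "Self-harm, encompassing acts of self-injury and overdose irrespective of suicidal intent [1"]. Overdose stands beside self-injury in that sentence, and intent is explicitly set aside.

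The inclusion criteria (Trial setting and participants) apply the definition from the same reference: "Engaged in self-harm, following the NICE definition [1], two or more times in their lifetime, with at least one episode in the past year". On how this is established, the article says: "This will be confirmed via the Self-Injurious Thoughts and Behaviours Interview Short Form (SITBI; [28"]). No other means of confirmation is named.

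The section on self-harm behaviour and urges then states the scope of the instrument: the SITBI short form "is a structured interview measure that will be used to assess suicide attempts and non-suicidal self-injury (NSSI"). One adaptation is specified. The opening NSSI question will take its wording from the revised SITBI, with more detail on what may count and "some examples of behaviours that would not count as NSSI including indirect forms of harm (e.g. starving oneself"). Overdose is not mentioned in either direction.

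Under Primary outcomes, the article expects either urges (ABUSI) or "behaviour, assessed via the Self-Injurious Thoughts and Behaviours Interview Short Form (SITBI; [28]), would be the primary outcome in a subsequent trial".

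**The concern.** The same interview decides who meets the self-harm criterion and measures self-harm behaviour afterwards, and its stated scope is narrower than the construct it serves. Two consequences follow if the description is taken as it stands.

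- **Outcome.** A non-suicidal overdose during follow-up has no designated place. It may be left out, or an assessor may place it under NSSI or under suicide attempts. The first lowers the count relative to the plan's construct. The second makes the components depend on who conducts the interview. Either way, what this trial passes on to a definitive trial about the behaviour outcome would not quite describe self-harm as the plan defines it.
- **Eligibility.** A young person could meet the written criterion and still fail its confirmation.

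The plan's own checks would not reveal the problem. The Outcome Suitability criterion in Table 1 looks at missing SITBI and ABUSI data at 16 weeks, and a behaviour that is never asked about does not show up as missing. Such episodes could not reliably be recovered once follow-up is over.

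**Working it through.** No figure in the plan depends on this point, so there is none to reproduce. The check sets the passages side by side.

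**Step 1: coverage.** The Introduction's definition has two methods and two states of intent, which gives four cells. Suicide attempts take the two cells with intent. NSSI, read in the Introduction's terms, takes self-injury without intent.

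| | With suicidal intent | Without suicidal intent |
|---|---|---|
| Self-injury | Suicide attempts | NSSI |
| Overdose | Suicide attempts | No stated place |

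**Step 2: does the adaptation fill the empty cell?** Not as described. It changes the opening NSSI wording, and the only example the article gives concerns what to leave out (indirect harm).

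**Step 3: does another measure fill it?** In Table 2 the SITBI is the only measure of self-harm behaviour. The ABUSI covers urges, and the ESIQ covers positive beliefs and dependence. Adverse event monitoring may pick up some overdoses, but it is neither the outcome nor the eligibility check. The safety section also expects events to be noticed more readily in the brief CAT arm, so it is not an even-handed substitute.

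**Step 4: size of any undercount.** Let p be the share of all self-harm episodes, on the plan's definition, that are overdoses without suicidal intent. Let f be the fraction of those that no SITBI section records.

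- Recorded count = true count × (1 − p × f), so the proportional undercount is p × f.
- Since f is at most 1, the undercount is at most p.
- The documents give neither p nor f. Purely as an illustration, if p were 5% the undercount would lie between 0 (f = 0) and 5% (f = 1). If p were 20% it would lie between 0 and 20%.
- At f = 0 all such episodes are coded somewhere. The sum of the components is then right, but its split between suicide attempts and NSSI may not be.

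**Step 5: who could be affected at eligibility.** Let A be the lifetime number of suicide attempts plus NSSI episodes, and B the number of these in the past year. A young person who truly qualifies fails confirmation only if A < 2 or B < 1 and non-suicidal overdoses make up the shortfall. With one NSSI episode and one non-suicidal overdose, A = 1 and confirmation fails. With several old NSSI episodes and a non-suicidal overdose as the only past-year episode, B = 0 and it fails. With A ≥ 2 and B ≥ 1 there is no effect, however many overdoses there were.

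**Step 6: effect on the plan's figures.** The target of 60 (30 per arm) rests on precision. The progression criteria concern recruitment, retention, missing data and therapy adherence. None of these thresholds changes.

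**The case against.** The best reply is that the deciding text is not in view. The article summarises the interview in a sentence, does not reproduce the revised NSSI wording, and offers the CRF on request. It never defines NSSI or excludes overdose from it, so interviewers may in practice record a non-suicidal overdose there. That stands. A reader might infer that the interview certainly omits the question, and the documents do not support that. They support only the statement that, as described, these episodes have no stated place. The reply does not dispose of the point, because the article's own terms separate overdose from self-injury and the described adaptation does not rejoin them.

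It is also fair to say that little in this trial turns on the matter. The article states that "inferential testing of treatment efficacy is therefore not the goal of the study", the SITBI is one of two candidate outcomes, and their suitability is still to be judged. How SITBI components are scored or combined may properly be left to the SAP. All of this limits the consequence. It does not remove the mismatch between the stated construct and the stated scope of the measure.

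Finally, an added item would lie outside the validated sections, and a sentence saying where such episodes are coded might be enough if the existing wording already captures them. The first part is a real cost. The second holds only if the adapted wording does capture them, which the article does not show.

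**Conclusion.** The mismatch stands on the article's own wording. Overdose without suicidal intent is within the plan's definition of self-harm but has no stated place in the eligibility check or in the only measure of self-harm behaviour. Such episodes may go unrecorded or be coded inconsistently.

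The size is unknown, with the share of episodes that are non-suicidal overdoses as its upper limit. A reader might go further and infer that the behaviour count will be too low by that whole share. That would require every such episode to be lost, whereas some may be coded under another section. A reader might also infer that a similar fraction of referrals would be misclassified. A share of episodes does not convert into a share of people failing a threshold, and the eligibility effect is confined to those who need these episodes to reach it.

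The conclusion assumes that NSSI is read in the Introduction's terms, with overdose distinct from self-injury. It would fall away if the adapted wording already included self-poisoning. No progression threshold or sample size changes. This is a cheap improvement to a candidate primary outcome and does not undermine the feasibility aims.

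**What to change.** Within the SITBI adaptation already planned:

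- add a stem and a count item for overdose or self-poisoning without suicidal intent, asked at baseline/screening and at 8, 16 and 20 weeks;
- use that item, together with suicide attempts and NSSI, when confirming the lifetime and past-year eligibility counts;
- report it as a separate component beside suicide attempts and NSSI, so that the validated sections stay intact and can still be read on their own.

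The cost is one or two extra CRF questions per assessment. The drawback is that they lie outside the validated SITBI sections, which is why the component should be shown separately.

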#### Dependence on self-harm

The Experiences of Self-Injury Questionnaire—Positive Beliefs subscale (ESIQ; [36]) is an 8-item questionnaire that measures positive beliefs and perceived dependency on self-harm. Scores range from 0 to 32 with higher scores indicating greater dependency. Research has supported the factor structure, validity, and reliability of this measure [36].

#### Depressive symptoms

The Patient Health Questionnaire—9 for adolescents (PHQ-A; [37, 38]) is nine-item self-report questionnaire that assesses depressive symptoms in young people over the past 2 weeks. Scores range from 0 to 27 with higher scores indicating worse symptoms. The PHQ-9 has been recommended as a screening measure for depression in young people with acceptable sensitivity and specificity [39]. The PHQ-A includes some adjustments to wording to make the measure more appropriate to young people [37, 38].

#### Internalising and externalising problems

The Strength and Difficulties Questionnaire self-report version (SDQ; [40, 41]) is a 25-item self-report questionnaire that assesses a range of difficulties in young people including internalising, externalising, and peer problems. A total difficulties score can be generated which ranges from 0 to 40, with higher scores indicating greater difficulties. The factor structure and validity of the SDQ have been supported and total score has good internal consistency [41].

#### Perceived recovery

The Recovery Questionnaire (ReQuestYP; [42]) is a questionnaire that assesses perceived recovery from mental health difficulties over the past week. Scores range from 0 to 90, with higher scores indicating greater recovery. The reliability and validity of the measure have been supported [42, 43].

### Health economics

The feasibility of collecting data necessary for a full economic evaluation will be assessed through the collection of service-use data and health-related quality of life (HRQL). The cost of providing the intervention and TAU will be estimated based on therapist-recorded service-use during the trial. A bespoke resource use questionnaire will be developed based on the adolescent Client Service Receipt Inventory (CSRI; [44, 45]) to capture details of other health and social care service utilisation. The Child Health Utility Instrument (CHU9D; [46]) is a nine-item measure of HRQL for 7- to 17-year-olds. Utility weights can be assigned to CHU9D descriptive health states and can then be used to generate quality-adjusted life years for use in economic evaluation. These measures will be completed at baseline and 20 weeks.

